### Design

The effectiveness of Boost Camp will be tested by a clustered randomized controlled trial (cRCT) with two conditions, e.g. an intervention and a control condition (see Fig. 1). Randomization is clustered by school, which reduces the risk of contamination.

**Fig. 1 Fig1:**
[figure not shown]
Study design

The outcomes will be measured by self-report questionnaires at the beginning of the school year (baseline: T0), immediately after Boost Camp (post -test: T1), at the beginning of the second semester (3FU, T2), and at the end of the school year (6FU, T3). Students in the control condition fill out the questionnaires in the same period as the intervention condition. Parent- and teacher-report questionnaires will be administered at baseline (T0) and at the end of the school year (T3). The trial is registered on the 13th of June 2017 at the ISRCTN Trial Register: ISRCTN68235634.

### The boost camp program

#### Theory

A well evaluated ER program is the Affect Regulation Training (ART) developed by Berking and Whitley [15]. According to this training, mastering the ART-sequence is necessary to regulate undesired affective states. The ART-sequence includes seven skills that must be acquired in a specific order, namely muscle relaxation, breathing relaxation, nonjudgmental awareness, acceptance and tolerance, compassionate self-support, analyzing emotions, and modifying emotions [13]. The ART program was designed as a stand-alone intervention to enhance adults’ adaptive ER skills by integrating techniques from various cognitive-behavioral treatment approaches, such as acceptance and commitment therapy, emotion focused therapy, mindfulness, problem solving therapies, and strength-focused interventions. ART has recently been shown to be effective in both clinical and non-clinical adult samples [12, 14–16, 26, 61].

Boost Camp is largely based on and inspired by ART. The program targets the same seven ER skills, but skills one and two are combined in one module, as well as skills six and seven (see Fig. 2). Further, important efforts were made to make the training more suited for children and adolescents. Two different pilot studies evaluated specifically step three (acceptance), four (self-support) and five (analyzing & modifying emotions) and found positive effects in young adolescents ([name], [name], [name] & [name]: The effect of a short emotion regulation training for young adolescents, unpublished).

**Fig. 2 Fig2:**
[figure not shown]
Boost Camp Modules. Adapted from “The Affect Regulation Training (ART): a transdiagnostic approach to the prevention and treatment of mental disorders,” by M. Berking and C. Lucas, 2015, *Current Opinion in Psychology*, *3*, p.66

The first skill, *relaxation*, refers to a behavioral technique for coping with increased levels of arousal which often coincides with negative emotional affect states [78, 89]. Relaxation techniques do not require much training and skills [83], whereby they easily can be used to facilitate adolescents’ ER efforts [98]. Decreasing the first arousal of an emotional experience is an important first step of ER as it enables an individual to accept, analyze, and modify the negative emotions. Progressive muscle relaxation [82] and breathing techniques [5] are widely used relaxation exercises in evidence-based health and children’s and adolescents’ stress regulation [21, 47, 113].

Second, *awareness* has recently been introduced as a specific ER skill that serves as a basis for learning other adaptive ER skills [15]. The aim is to focus attention on the present and observe emotions in a non-judgmental way. Hypersensitive interpretation- and appraisal processes are hereby being interrupted, which is a basic but crucial step before using cognitive resources to regulate own emotions [15]. To the best of our knowledge, awareness is not evaluated as a stand-alone technique. However, as component evidence-based programs, it has proven its merit [4, 64, 120, 137].

Third, a*cceptance* can be described as making the best of the situation. Acceptance of aversive events decreases the urge to follow inflexible patterns of avoidance, which is often known as an automatic response to escape and/or avoid aversive emotions, thoughts and body experiences [73–75]. Low levels of acceptance have been associated with different psychological problems, such as symptoms of anxiety and depressions [41, 58, 145]. Although it is stated that including a module acceptance has the potential to improve the efficacy of prevention programs [17], to date, only a couple of studies evaluated prevention programs targeting acceptance in adolescents, with mixed results. The efficacy of acceptance was examined in two school-based prevention programs among students aged 13 to 20 years. Results showed large effect sizes for the reduction in stress complaints, and medium effect sizes for the reduction in depression and anxiety scores [25, 111]. Another study evaluated the feasibility of an ACT-based prevention program among high school students aged 14 to 16 years, but found no statically significant differences between the intervention and control condition. Nevertheless, these results indicated that the intervention was feasible in a school context and suitable for the students [25].

Furthermore, *self-supporting* skills refers to satisfying basic (i.e. safety and love needs) and esteem needs (i.e. needs for self-confidence, self-esteem, self-compassion and achievement) [94], activating a strong mindset about one’s ability and personality, in order to facilitate emotional processing. A specific and well-known ER strategy that can be considered self-supporting is *distraction*, which is defined as intentionally shifting attention away from the negative emotion to an external stimulus [65]. When experiencing negative emotions, self-thoughts are often characterized by high levels of self-criticism and rejection. Consequently, additional negative feelings arise and significantly reduce the capacity to effective regulate the initial negative emotion [15]. Paying attention to an external stimulus reduces the change of the development of those additional negative feelings. Evidence for this strategy in adolescents is rather mixed, with some studies reporting positive effects (e.g. self-reported distraction is negatively associated with depressive symptoms [76]) or counter-productive outcomes (e.g. distraction is seen as cognitive avoidance, a maladaptive strategy to perceive control about a situation) [39]. Nonetheless, distraction has been shown to be effective in immediately improving adolescents’ emotional outcomes (i.e., reducing negative affect and increasing positive affect) after a negative mood induction [77, 143, 144], and combining distraction with acceptance of problem solving is thought to improve long-term effects [48, 149]. Another less-known strategy that recently is introduced as an effective ER strategy is *compassionate self-support* [15]. Self-compassion can be described as creating distance from and taking an external perspective on the suffering self and transform feelings of pain and suffer into feelings of kindness and understanding, in order to create the empathic wish to help themselves [15, 101].

The fifth and ultimate skill is to actively *analyze & modify the emotional experience* [15]. For this, two well-studied adaptive ER strategies can be used. One strategy is *cognitive reappraisal*, which can be defined as thinking in a more positive way about the affective stimuli or events [66]. Cognitive reappraisal shows good effects in decreasing an induced negative mood and increasing an induced positive mood [45, 114], and has long-lasting positive effects on emotional well-being [87, 95, 104, 124]. Training cognitive reappraisal is often a core element in various effective CBT programs for mood and anxiety disorders in both adults, adolescents and children [8, 93, 100], consistent with the observation that individuals in an anxious or depressed mood use less cognitive reappraisal compared to non-clinical samples [29, 45, 59, 107]. However, this strategy might only be effective when the level of arousal and negative emotion is mild to moderate [95]. Therefore, it can be hypothesized that cognitive reappraisal is particularly effective when it is preceded by strategies such as acceptance or distraction which actively decrease the level of arousal and emotion.

A second strategy that can be utilized to analyze and modify emotion is *problem solving,* which refers to actively modifying the stressors that induce negative affect in order to change the associated emotions. Typically, problem solving involves several steps to adequately solve a problem which may include a positive problem orientation, problem formulation, solutions generation, alternatives evaluation and process evaluation [42, 103]. Adolescents poor problem-solving skills have been associated with problem behavior [123], suicide risk [67], depressive- and anxiety symptoms [10, 115, 123, 125]. Studies that evaluate the effects of problem solving as a single and explicit ER strategy in youth are scarce. Hilt and Pollak [77] studied problem solving in a non-clinical sample of adolescents and found that the use of problem-solving did not influence induced ruminative states. However, the authors emphasize that problem-solving may have stronger effects on rumination when it is preceded by the use of distraction. Furthermore, training adolescents’ problem solving skills is often a component of cognitive-behavioral therapy (CBT) programs [43], which have been showed effective for treating various psychological disorders, such as depression [9, 20] and anxiety [140].

#### Content and structure of the boost camp program

In *the intervention condition* students are trained in five basic skills for adaptive ER (see Fig. 2).

*Day one* starts with an introduction, which aims to create a safe environment and to meet the trainers and the program. This is followed by a brief psycho-education session on different emotions and their relation with thoughts and behavior. Then, students are informed about the rational of using *relaxation- and awareness* practices and they are challenged to perform the corresponding exercises such as breathing exercises, progressive muscle relaxation, and a body scan. Next, class games are being played to learn about the different functions of emotions, which contribute to the facilitation of *accepting* and restraining intense negative emotions. Next, those functions are used to create ‘tolerance sentences’, which makes it easier to accept negative emotions and can be easily transferred to real situations. Finally, the students will be taught how to *support themselves*. First, information about the self-esteem concept and its association with mental health is given, followed by individual and group exercises to boost the students’ self-esteem. Second, students are informed about the importance of distraction and through group discussion effective distraction activities are listed. Lastly, students are challenged to create positive self-talk sentences to become a strong mindset about their ability and personality. To finish, a group activity is organized to create a frog out of paper and cardboard on which students can write their favorite sentences and take home, in order to make the transfer of the learned skills to daily life easier.

After a brief active recapitulation about the skills from day one, *day two* is fully devoted to learn how to analyze and modify an emotional experience. First, the strategy *cognitive reappraisal* is taught*.* Students learn how to be aware of their own thoughts, categorize them as helpful, unhelpful or neutral, and produce emotion and situation specific helpful thoughts through exercises and role-play. Second, students will learn and exercise the different steps to *active solve their problem*. All information, exercises and games were based on evidence based protocols [15, 18, 20, 46, 71, 131, 140] and put together in a child friendly work. Finally, t*he two boostersessions* are administered to refresh learned skills by individual- and group exercises. Both sessions takes place at school during four school hours.

#### Delivery

We planned to divide every class into two subgroups of maximum ten adolescents and with two trainers each. Groups in the B grade (i.e. children with special needs) will consist of six participants each. The training is coordinated by two main researchers ([name]) from Ghent University and delivered by five masters in clinical psychology and nine psychologists with at least a bachelor’s degree in clinical psychology. All trainers attend an intensive 1-day ‘train-the-trainers’ workshop and will be provided with a group leader manual, containing the different protocols for every step [142], approved by the Ethical Committee. The protocol will not be changed, at least not until the end of this data-collection. The two main researchers trained and supervised the process. They also stay on call by phone or email for support and help when needed as long as the program is active.

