### Goals and hypotheses

The present study has three main goals. First, this study will test the effectiveness of a new school-based universal prevention program “Boost Camp”, targeted at strengthening ER skills in the stressful first year of high school. It is hypothesized that Boost Camp will improve or maintain emotional wellbeing. More specifically, it is hypothesized that Boost Camp will lead to an *increased* use of adaptive ER, *more* positive affect, a *higher* self-esteem, and a *better* quality of life in participants in the intervention condition compared with adolescents in the control condition. Moreover, *less* negative affect, *less* use of maladaptive ER and *less* depressive and anxiety symptoms will also be seen as markers of wellbeing.

Second, this study will test the effects of the program on secondary outcomes. It is hypothesized that Boost Camp will lead to *better* peer relations, *less* negative mental health attitudes, an *increase* in academic achievements, a *smaller* amount of school absenteeism and *less* school drop-out. Third, this study will examine the moderating role of child characteristics such as EF, baseline level of psychological problems, and gender. It is hypothesized that the program will be *less* effective for young adolescents with lower levels of EF and *more* effective for young adolescents with a higher baseline level of psychological problems. Finally, due to the difference in experiencing difficulties and psychological distress within the transition phase, the program is expected to have better effects for girls than for boys.

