## Methods

### Participants and procedure

Six secondary schools in the East of Flanders are contacted to participate in the study. Participants are adolescents in their first year of secondary school (7th grade, ages 11–13). The aim is to reach 300 students spread over 16 classes. We ensure the inclusion of students from different Socio Economic Status (SES) groups and various educational levels to compose a heterogeneous sample. In Belgium, there are two educational levels in secondary school. The first education level, grade A, is considered as a broad first grade in which students receive basic knowledge on technics, mathematics, or languages, with the intention to prepare them on a more specific educational program in the second grade. The second education level, grade B, is intended for students with specific needs. Both are included.

Schools that are interested are asked to participate with as many first-grade class groups as possible. If they give their consent to take part in the study, they are randomized by the researcher in a intervention or a control group. Finally, six rural schools with comparable background and meeting the same language criteria decided to participate in the study. All schools receive information letters for students and their parents, which contain detailed information about the study aims and procedure. Parents can either give or withhold their permission for including their child’s data in the study, and both parents and children are free to withdraw from the study at all times. The Boost Camp program is incorporated in the class curriculum, so all participants in the intervention condition receive the program. The advantage of incorporating the program in the class curriculum is that all adolescents participate and interact. To ensure that the intervention and the control schools place an equal emphasis on students’ mental health, teachers of all participating schools receive a workshop on care management and are invited to sign a school charter on the importance of emotional well-being of the schoolchildren.

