Assumptions will be checked by examining descriptive statistics and missing variables will be examined. When data are missing completely at random, maximum likelihood estimation will be used to estimate the missing values. When data are not missing completely at random, generalized estimating equation analyses will be used. Possible baseline differences in both groups will be assessed using simple t-tests or chi-square tests, and variables that show baseline differences will be entered as covariates of no interest in all models. To assess the difference between the intervention and control condition in the change in the use of adaptive ER skills and in emotional wellbeing during 6 months following the program, a mixed model will be used. More specifically, a mixed model with fixed effects for condition (intervention or control), time (immediately after intervention, 2 months post FU, and 6 months post FU), and their interaction, adjusted for baseline will be used. Moderators will be added one by one. To account for the nested structure of students within classes, and classes within schools, a random intercept for schools and a random intercept for classes nested within schools will be utilized. To account for the temporal correlation of measurements within a student, an unstructured residual covariance will be assumed.

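### Educational level (grade A or B) is no prespecified model term; it enters only if a baseline test shows an arm difference, and never as level-by-condition

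*Protocol article*

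**What the plan says.** The Participants and procedure section of the protocol article makes the mixture of levels deliberate: "We ensure the inclusion of students from different Socio Economic Status (SES) groups and various educational levels to compose a heterogeneous sample". It then says of the two streams: "The second education level, grade B, is intended for students with specific needs. Both are included".

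The Delivery section sets the general training format: "We planned to divide every class into two subgroups of maximum ten adolescents and with two trainers each". For the other stream it says: "Groups in the B grade (i.e. children with special needs) will consist of six participants each". Only the intervention arm is trained, so this difference exists only there.

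On allocation, schools that consent are told that "they are randomized by the researcher in a intervention or a control group", and the Design section adds: "Randomization is clustered by school, which reduces the risk of contamination". The six schools are described as alike in background and language. Nothing is said about their educational levels.

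The Data analysis section specifies a mixed model with condition, time and their interaction, adjusted for baseline, with random intercepts for school and for class within school. Arms are compared at baseline by t-tests or chi-square tests, and any variable that differs becomes a nuisance covariate in all models. The listed moderators are initial psychological problems (CBCL), EF (BRIEF) and gender. For these, "Moderators will be added one by one". Level is named neither as a covariate nor as a moderator.

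**The concern.** Level is a known design feature of every class. It is plausibly related to the outcomes and to two of the three moderators, and it decides how the program is delivered. Leaving it to a baseline test has two consequences.

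First, adjustment of the main comparison depends on whether that test happens to reach significance, so a moderate imbalance can go unadjusted.

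Second, the third study goal predicts less benefit with weaker EF and more benefit with more baseline problems. If either trait is commoner in grade B, the moderator-by-condition term also carries whatever difference in effect comes from level and from the smaller groups. A rule triggered by differences between arms does not address this.

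**Working it through.** The article states no figure on this point, so there is nothing to reproduce. Grade B shares, their spread over schools and the A/B outcome gap are assumptions throughout.

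**1. How often could grade B fall in one arm?** There are six schools. A 3:3 split gives C(6,3) = 20 allocations. A 4:2 split gives C(6,2) = 15; it is included because the sample-size text plans 3:2 in favour of control.

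| Schools with grade B (assumed) | All in one arm, 3:3 | All in one arm, 4:2 |
|---|---|---|
| 1 | certain | certain |
| 2 | 2 × C(4,1) = 8; 8/20 = 0.40 | 6 + 1 = 7; 7/15 = 0.47 |
| 3 | 2/20 = 0.10 | 3/15 = 0.20 |
| 4 | 0 | 1/15 = 0.07 |

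**2. Would the baseline rule catch the extreme case?** Take 45 of 150 grade B pupils against 0 of 150. The pooled share is 0.15, so z = 0.30 / √(0.15 × 0.85 × 2/150) = 0.30/0.0412 ≈ 7.3. If level is among the variables tested, it enters every model.

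**3. Would it catch a moderate imbalance?** Arm sizes are 117 (intervention) and 174 (control), from the Data analysis section. Power = Φ[(d − 1.96 × SE0)/SE1], where d is the difference in grade B share, SE0 the pooled and SE1 the unpooled standard error. Clustering is ignored, as in the simple test planned.

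| Shares (117 vs 174) | SE0 | SE1 | Power | Power at 150/150 |
|---|---|---|---|---|
| 10% vs 20% | 0.0438 | 0.0411 | 0.63 | 0.68 |
| 20% vs 30% | 0.0524 | 0.0507 | 0.48 | 0.52 |
| 10% vs 15% | 0.0402 | 0.0388 | 0.23 | 0.26 |

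These treat the shares as underlying values. If they are the realised shares, the test result is fixed: z = 0.10/0.0438 = 2.28 (flagged), 0.10/0.0524 = 1.91 (missed) and 0.05/0.0402 = 1.24 (missed). On either reading, a difference of about ten percentage points may or may not trigger adjustment.

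**4. What would a missed imbalance cost?** The shift in an unadjusted contrast is the difference in grade B share times the A/B gap. For ten points and an assumed gap of 0.2 to 0.5 SD, it is 0.10 × 0.2 = 0.02 to 0.10 × 0.5 = 0.05 SD. The planned model adjusts for baseline. With an assumed baseline slope of 0.6 and the same gap at both times, a fraction 1 − 0.6 = 0.4 remains, about 0.008 to 0.02 SD.

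**5. The moderator models.** Let δ be the difference in intervention effect between grade B and grade A (group size included), and λ the slope of level on EF. If level-by-condition is omitted, the EF-by-condition coefficient is shifted by roughly δ × λ. Adding level as a main effect does not remove this, because the omitted term is the product of level and condition. The shift is also present when the arms are perfectly balanced on level, in which case the baseline rule would not bring level in at all. The class random intercept may take up part of it. The article gives neither δ nor λ, so no size can be attached.

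**The case against.** The strongest reply is that the plan already has a rule for this. Any variable that differs at baseline goes into all models, moderator models included, and step 2 shows that it would catch the worst case easily. That stands. It would be wrong to say that level can never be adjusted for. The rule remains conditional, however, and supplies a main effect only.

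A reader might infer that the school allocation is unbalanced on level, since no restriction is described. The documents do not support this. A condensed article may leave out such detail, the distribution of grade B is not given, and if four or more schools have grade B classes a 3:3 split cannot put them all in one arm. The Strengths and limitations section itself admits that randomising schools risks differing pupil characteristics.

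A reader might also infer that group size confounds the main comparison. It does not: it varies only within the intervention arm and is part of the program as delivered.

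Two further objections stand in part. No text says that weak EF is concentrated in grade B; that is a plausible assumption. And level-by-condition cannot be estimated if grade B falls in one arm, while moderation within level answers a different question from moderation across the recruited sample. The interaction therefore belongs in a sensitivity analysis and should not be an unconditional requirement.

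**Conclusion.** The point holds in a limited form. Both levels are included, they are trained in different group sizes, and level is prespecified in no model. The conditional rule catches gross imbalance but is unreliable for a moderate one, with power from about 0.23 to 0.63 over the assumed shares. The likely effect of a missed imbalance on the main contrast is small: 0.02 to 0.05 SD unadjusted in the illustration, and less after the planned baseline adjustment.

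The moderator side matters at least as much, because no outcome of the baseline rule yields the term that separates EF or CBCL moderation from level and group size. It would be too strong to say that this masks or reverses the hypothesised moderation. That depends on the grade B share, the A/B difference in EF and problems, and the A/B difference in effect, none of which is given.

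**What to change.** 1. Enter educational level (A/B) as a prespecified fixed covariate in every outcome model, whatever the baseline test shows.
2. Where both arms contain grade B classes, add level-by-condition to the EF and CBCL moderator models as a sensitivity analysis, and report it beside the planned model.
3. State that any A/B difference in effect includes the difference in training group size, so the two cannot be told apart.

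The cost is one class-level term in the main models. Level follows from the class, so no new data are needed and the change is possible after allocation. In the sensitivity analysis the intervals for the EF and CBCL interactions will widen, possibly a great deal if few of the 16 classes are grade B. If grade B turns out to be in one arm only, step 2 is dropped and that should be reported; the level term in step 1 then makes the arm comparison rest essentially on grade A pupils.
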